## Abstract

**Background:**

Controlling hypertension rates and maintaining normal blood pressure, particularly in resource-constrained settings, represent ongoing challenges of effective and affordable implementation in health care. One of the strategies being largely advocated to improve high blood pressure calls for salt reduction strategies. This study aims to estimate the impact of a population-level intervention based on sodium reduction and potassium increase – in practice, introducing a low-sodium, high-potassium salt substitute – on adult blood pressure levels.

**Methods/Design:**

The proposed implementation research study includes two components: Phase 1, an exploratory component, and Phase 2, an intervention component. The exploratory component involves a triangle taste test and a formative research study designed to gain an understanding of the best implementation methods. Phase 2 involves a pragmatic stepped wedge trial design where the intervention will be progressively implemented in several clusters starting the intervention randomly at different times. In addition, we will evaluate the implementation strategy using a cost-effectiveness analysis.

**Discussion:**

This is the first project in a Latin-American setting to implement a salt substitution intervention at the population level to tackle high blood pressure. Data generated and lessons learnt from this study will provide a strong platform to address potential interventions applicable to other similar low- and middle-income settings.

**Trial registration:**

This study is registered in ClinicalTrials.gov NCT01960972.

## Background

Hypertension is a silent condition and a major worldwide contributor to the growing pandemic of cardiovascular disease (CVD) and stroke, especially in low- and middle-income countries (LMIC) [1-3]. Poor control rates for hypertension and appropriate strategies to maintain normal blood pressure, particularly in resource-constrained settings, reflect the challenge of effective and affordable implementation in health care systems.

One of the policies being advocated by both international technical organizations and academic leaders is the implementation of salt reduction strategies [4,5]. This approach is applicable not only to LMIC but also established economies. The Institute of Medicine labeled hypertension as a ‘neglected disease’ and recommended salt-reduction strategies at the population level as the way forward [6,7].

A decade ago, the Prospective Studies Collaboration conducted a meta-analysis of 61 observational studies of blood pressure and vascular disease in adults and found that for each 2 mmHg decrease in systolic blood pressure, stroke mortality and cardiovascular mortality decreased by 10% and 7%, respectively, an effect that was observed in reductions of systolic blood pressure levels up to 115 mmHg [8]. This indicates that small changes in blood pressure at the population level could result in large public health gains. The main challenge, however, is how best to introduce and achieve these changes under real life conditions while acknowledging the potential impact of local contexts.

Sodium chloride has been the subject of intense scientific research aimed at understanding its impact on health, especially on blood pressure [9-14]. Although criticized because of a biased approach [15], the Committee on the Consequences of Sodium Reduction in Populations convened by the Institute of Medicine reported that existing studies that explore the impact of salt reduction strategies on health are less than optimal [6]. A recent systematic review assessing the effect of modest reduction in salt intake on blood pressure supports the need of reducing salt [10]. Two previous studies, one in Tibet [16] and another in rural China [17], have demonstrated the potential effect of salt substitution on blood pressure among individuals with diagnosed hypertension; however, to our knowledge, limited evidence regarding this effect is available at the population level.

The most recent WHO guidelines regarding sodium intake for adults and children [18] strongly recommend a reduction to less than 5 grams/day of salt among adults with or without hypertension. Yet, the successful implementation of this recommendation, especially in developing countries, might be difficult to achieve without taking into account the role of salt on palatability of foods associated with taste [19,20]. In Peru, no accurate data exists about the sources of salt consumption [21]. Based on our pilot studies, salt added during cooking, rather than processed foods, appears as the main source of salt intake. Monitoring salt intake in both developing and developed countries poses major practical challenges [22]. In the Peruvian context, salt reduction strategies do have a role and should be addressed through their own channels. Such an approach does not conflict with salt substitution interventions, since cooking practices are highly prevalent and thus amenable to achieve changes in patterns of overall salt intake.

This study protocol addresses both ongoing scientific and practical implementation challenges by estimating the impact of a population-level intervention based on reducing sodium and increasing potassium – in practice, introducing a low-sodium, high-potassium salt substitute – on adult blood pressure levels. The information gathered in this study will provide strong, locally relevant information that may be applicable to other similar settings in Latin America and elsewhere.

## Methods/Design

### Objectives

This study aims to bridge a gap in implementation research by reducing blood pressure levels at the population level through the introduction of a community-wide intervention with a low-sodium, high-potassium salt substitute in a resource-constrained setting. Accordingly, the specific objectives of this study protocol are: i) to assess patterns of predisposition towards incorporating a salt substitute into daily cooking among villagers, authorities, and other potential stakeholders, in order to inform the structure of the intervention in the local communities and ensure successful implementation; ii) to implement and assess the impact of an intervention using a salt substitute on blood pressure at the population level using a stepped wedge trial design; and iii) to determine, if successful, the cost of this implementation and the incremental cost-effectiveness ratio of our intervention.

### Study design

The proposed implementation research study includes an exploratory component and a field intervention component. The intervention involves a pragmatic stepped wedge trial design, such that we will progressively implement our intervention at random in several clusters [23] following an introductory period oriented to gaining an understanding of the best implementation methods. The study will include both qualitative and quantitative methodologies for collecting baseline information, and monitoring the impact of the intervention during rollout and at its conclusion.

### Setting and time frame

This study involves inhabitants from Tumbes, a department located in the north coastal region of Peru on the border with Ecuador. The semi-urban area of Tumbes consists of more than 100 villages of varying size with an approximate total population of 80,000. It is comprised of a large ‘mestizo’ – mixed of European and Amerindian ancestry – population, and the traditional agricultural and fishing landscape has become intermixed with rapidly growing urban sections. Illiteracy rate is around 10%, and 50% of the inhabitants have no health insurance. Activities related to this protocol began in 2012 and are expected to continue through 2017.

### Participant recruitment and selection criteria

Participants from six randomly-selected villages will be involved in the different phases of the study. Potentially eligible subjects will be identified from the most updated census available. Males or females aged 18 years and over from the randomly selected villages, capable of understanding study procedures, capable of providing informed consent, and full-time residents in the area are eligible. Only those participants with mental illness that impair their consent will be excluded. In the case of the stepped wedge trial, self-reported history of chronic kidney disease and heart disease will be considered as additional exclusion criteria.

### Procedures

To accomplish the proposed objectives, this protocol has two phases:

#### *Phase 1: Exploratory phase*

This component includes a triangle taste test and a formative qualitative research study that will generate the elements to create a social marketing campaign before the intervention’s implementation.

##### 

**Triangle taste test** This test is a discriminative form of a sensory analysis that may indicate whether or not a detectable difference in taste exists between two samples [24]. Common salt, 100% sodium chloride, will be compared to salt substitute samples containing different potassium chloride concentrations: 25%, 33%, and 50%, with the consequent reduction in sodium. This experiment will allow the assessment of acceptability of taste of the salt substitutes compared to common salt. Participants will be exposed to three coded food samples, two identical and one different (odd). Subjects will taste each sample in a random order, to avoid positional bias, and will be instructed to identify the odd sample [25].

##### 

**Formative research** This component will combine focus groups and in-depth interview research techniques with a wide range of participants from the community including inhabitants, commercial traders, and stakeholders such as staff from the health care system as well as local authorities. In this way, we will guarantee a diversity of points of view regarding ordinary salt, high blood pressure, and CVD to create an appropriate marketing campaign to increase the likelihood of the acceptance of the salt substitute. The focus groups will include inhabitants from different villages, while in-depth interviews will be conducted with individuals with hypertension and stakeholders. The stakeholders include, but are not limited to, community health leaders and health promoters, local authorities (village representatives, health authorities, etc.), health workers (physicians, nurses, and health technicians), and commercial traders (restaurant owners, street vendors, community kitchen members, bakers, shopkeepers, etc.).

##### 

**Social marketing campaign** The goal of this campaign is to introduce participants to the salt substitute prior to and during the intervention in order to enhance its acceptance. Thus, villagers and stakeholders will be actively invited to develop and later be exposed to social marketing techniques designed to encourage the salt substitute consumption.

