### Statistical analysis

#### *Triangle taste test*

We will be able to determine whether the total number of correct responses for the total number of participants is statistically significant based on the critical number of correct responses in a triangle taste test. Thus, there is a one out of three chance that the correct (odd) sample will be picked just by chance (guessing). We will then compute a z-statistic based on the following formula:

$$z=\frac{\left(k-\left(n/3\right)\right)}{\sqrt{2n/9}}$$

In this formula, ‘n’ is the total number of subjects assessed and ‘k’ is the number of correct responses [32]. Based on these results, we will reject the hypothesis of ‘no difference’ between samples if the number of correct responses is significantly greater than the calculated value (z).

##### 

**Qualitative data** Information from focus group sessions and in-depth interviews will be recorded and transcribed. All the collected information will be segmented, entered, coded, and analyzed using Atlas.Ti to identify a list of relevant themes and thus, identify key concepts to create our social marketing campaign. Coding will be carried out using the grounded theory approach to data analysis, where the data emerges from the participants, not the researchers [33,34]. The analysis will compare the information obtained from different subgroups of participants in order to identify and describe the similarities and divergences between men and women, patients from different age groups, and health workers and stakeholders. The analysis will also include notes from the field, i.e., fieldwork diary and minutes of the researchers’ meetings.

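### The triangle taste test shows whether a salt substitute can be told from common salt; the article says it will assess acceptability of taste

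*Protocol article*

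**What the plan says.** The paragraph on the triangle taste test (Protocol article, Phase 1: Exploratory phase) opens with what the method measures: "This test is a discriminative form of a sensory analysis that may indicate whether or not a detectable difference in taste exists between two samples". Common salt is to be compared with "salt substitute samples containing different potassium chloride concentrations: 25%, 33%, and 50%, with the consequent reduction in sodium". The paragraph then states the purpose: "This experiment will allow the assessment of acceptability of taste of the salt substitutes compared to common salt". The response asked of each participant comes last: they "will be instructed to identify the odd sample".

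The sample size section plans this test on the probability of a correct pick, 33% by guessing against 50%, with 5% significance and 90% power, and arrives at about 146 participants. The statistical analysis section computes a z-statistic from the number of tasters and the number of correct picks, and gives the decision rule: "we will reject the hypothesis of ‘no difference’ between samples if the number of correct responses is significantly greater than the calculated value (z".

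**The concern.** Detectability and acceptability are different properties. A person may notice that a substitute tastes different and still be content to cook with it, or may even prefer it. Another may notice and dislike it. Both count as one correct pick. The paragraph names the first property when it defines the test and the second when it says what the test is for, but the response and the analysis deliver only the first.

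What is at stake is the sentence that Phase 1 will eventually report. If detectability is read as acceptability, a significant result may be taken to mean that the taste is unacceptable, and a non-significant one that it tastes the same or is acceptable. The described data support neither.

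**Working it through.** **Inputs.** Chance probability 1/3, alternative 50%, significance 5%, power 90% and about 146 participants (sample size section); z = (k − n/3)/√(2n/9), with k correct picks among n tasters (statistical analysis section).

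**The article's own figure.** For 1/3 against 1/2 with one-sided 5% and 90% power:
- A two-sample comparison of proportions gives 148 per group (142 with 0.33 against 0.50), close to 146.
- The one-sample formula that matches the article's z-statistic gives [(1.645 × √(2/9) + 1.282 × √(1/4)) / (1/6)]² = 72.2, so 73.

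The figure of 146 is therefore reproduced only by a two-sample type of formula. The present point does not depend on it; 146 is used below only as the number of tasters.

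**Assumptions for the illustration.** The article does not say whether the test is one-sided (the wording of its decision rule suggests so), nor whether 146 is the total or the number per concentration. I take one-sided 5% and 146 tasters per comparison. I also use the usual guessing model, in which a proportion d always finds the odd sample and the rest guess: P(correct) = d + (1 − d)/3, so d = (P − 1/3)/(2/3). Under it, the planning value of 50% correct corresponds to d = (1/2 − 1/3)/(2/3) = 25%.

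**Just significant: 59 correct.**
- z = (59 − 48.67)/√(2 × 146/9) = 10.33/5.70 = 1.81. The exact binomial tail probability is 0.044, and 59 is the smallest count with a tail of at most 5%.
- Estimated discriminators: (59/146 − 1/3)/(2/3) = (0.404 − 0.333)/0.667 = 10.6%.
- Exact one-sided 95% bounds on P(correct) are 0.336 and 0.475, so d lies between 0.4% and 21%.

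**Just not significant: 58 correct.**
- z = (58 − 48.67)/5.70 = 1.64.
- Estimated discriminators: (0.397 − 0.333)/0.667 = 9.6%.
- The exact one-sided 95% upper bound on P(correct) is 0.468, so d may be as high as (0.468 − 0.333)/0.667 = 20%. The lower bound, 0.329, is below chance, so d may be zero.

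The two results carry almost the same information about discriminators, yet fall on opposite sides of the test.

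**Clearly significant: 73 correct (50%).** z = (73 − 48.67)/5.70 = 4.27. The value is the same whether those who detect the substitute like it or dislike it.

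**Other assumptions.**
- With 2.5% in the upper tail, the threshold at 146 tasters moves to 61 correct: (61/146 − 1/3)/(2/3) = 12.7% discriminators.
- If 146 were split over the three concentrations (146/3 is about 48 or 49), the one-sided 5% threshold with 48 tasters is 22 correct: (22/48 − 1/3)/(2/3) = 18.8% discriminators.

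The figures shift, but under none of these assumptions does the count carry information on liking.

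**The case against.** The strongest reply is that the sentence speaks of acceptability in comparison with common salt. If people cannot tell the substitute from common salt, its taste may fairly be presumed as acceptable as that of common salt. This has some force: with 146 tasters in one comparison, the exact power at 50% correct (25% discriminators) is 0.992, so a non-significant result would make discrimination on that scale unlikely. But the inference runs in one direction only. It needs a conclusion of similarity, whereas the planned test is of no difference and no similarity margin is described. For a concentration that is detected, it gives no answer at all.

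It can also be said that the sentence only states a purpose, and that the definition, the sizing and the hypothesis are all framed correctly as detection. That is true. The article nowhere says that a count will be read as acceptable or unacceptable. It keeps the point small but does not remove the mismatch.

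Several stronger readings are tempting and are not supported:
- A reader might infer that a formulation could be wrongly discarded or passed, with effects on uptake and blood pressure. The article states no rule that selects a concentration from this test, and the stepped wedge analysis does not use its result.
- A reader might infer that liking was not recorded. The article is condensed; one can say only that no such response is described.
- A reader might infer that the focus groups and interviews supply the missing measure. They bear on predisposition and on the marketing campaign, but no tasting or rating of the substitute is described there.

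**Conclusion.** The point holds as a matter of stated inference. As described, the test can show that a difference from common salt is detectable, and the correct picks can be turned into an estimate of how many people detect it. It cannot show acceptability in either direction. The mismatch itself rests on the article's own text and needs no calculation. The illustrative figures (about 11% discriminators at the first significant count, up to about 20% at the last non-significant one) rest on the guessing model, a one-sided 5% test and 146 tasters per comparison. They show how little a significance label says even about detection; they do not measure the size of any error about acceptability. The consequence is minor and confined to what Phase 1 may conclude.

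**What to change.** Restate the purpose in the Phase 1 paragraph as whether a difference in taste from common salt is detectable. For each potassium chloride concentration, report the number of tasters, the proportion of correct picks, and the estimated proportion of discriminators with its confidence interval, naming the guessing model. Say explicitly that a non-significant count does not show that the products taste the same or that the substitute is acceptable, and that a significant count does not show it to be unacceptable. Claim acceptability only from data that record it; if the focus groups or interviews did collect views on the taste of the substitute, cite them for that purpose.

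The cost is one reworded sentence and one derived estimate per concentration from data already collected. The Trial status section says Phase 1 is complete, so no procedure changes, only its reported conclusion.

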#### *Phase 2: Intervention and implementation activities*

##### 

**Baseline data collection** This information will be collected immediately before implementing activities in all participant villages. We plan to collect baseline information of participants at the individual- and family-level. We will use a modified version of the WHO STEP approach questionnaire for surveillance of non-communicable diseases [26]. Questions related to salt intake have also been included in these instruments. Ideally, salt intake should be assessed in urine and this is a limitation of our pragmatic design. We will indirectly evaluate salt intake consumption patterns by weighing salt containers in households. In addition, this baseline will include a clinical assessment to measure blood pressure in triplicate using standardized procedures with automated validated devices, and weight and height using standardized techniques and procedures. Costs-related data will also be collected at baseline in order to inform cost-effectiveness analysis at a later stage. A summary of the data collected at baseline is shown in Table 1.

**Table 1 T1:** Sections and topics of the questionnaire in the study

**Section**	**Components**
Demographic assessment form:	- Place and date
	- Consent process
	- Contact information
Sociodemographic information form:	- Demographic information
	- Health coverage
Household information form:	- Family characteristics
	- Expenditures
	- Change attitudes
	- History of blood pressure measurements
Knowledge about salt and high blood pressure:	- Knowledge about high blood pressure
	- Salt consumption
	- Household information: assets
Lifestyles assessment form:	- Smoking
	- Alcohol consumption
	- Food consumption
	- Physical activity
	- Lack of activity
Mental health assessment form:	- Depressive symptoms
	- Quality of life
	- Stress
	- Sleep patterns
Cardiovascular assessment form:	- Cardiovascular medication
	- Personal and familiar history
	- Memory
	- Stroke
Clinical measurements form:	- Height
	- Weight
	- Waist and hip circumference
	- Blood pressure
Costing data form:	- Patient costs
	- Program costs

##### 

**Intervention and implementation activities** Salt replacement will be progressively implemented over six months in each village. The intervention will contemplate interactions with families as well as bakeries, community kitchens, food vendors including street vendors, and restaurants. Ideally, replacement will require a complete exchange of ordinary salt. The assessments of salt consumption will be carried out using questionnaires and weighing of salt containers at randomly selected households over time, and also by evaluating supply chain management indicators such as rate of delivery of the salt substitute to each family or food vendors.

Because of logistical constraints, especially around introducing and sustaining an adequate social marketing campaign together with the salt substitute delivery, the intervention can only be implemented in stages. Thus, the stepped wedge trial is an optimal design to ensure both moral and social acceptability. As described by Brown [23], “*in a stepped wedge design, an intervention is rolled-out sequentially to participants (either as individuals or clusters of individuals) over a number of time periods. The order in which the different individuals or clusters receive the intervention is determined at random and, by the end of the random allocation, all individuals or groups will have received the intervention. Stepped wedge designs incorporate data collection at each point where a new group (step) receives the intervention*”. In Table 2, villages receiving the intervention are indicated with the number 1, and those villages not receiving the intervention are indicated with a 0.

**Table 2 T2:** Stepped wedge design for the proposed study

**Clusters**	**Time period**						
	**1**	**2**	**3**	**4**	**5**	**6**	**7**
Village 1	0	1	1	1	1	1	1
Village 2	0	0	1	1	1	1	1
Village 3	0	0	0	1	1	1	1
Village 4	0	0	0	0	1	1	1
Village 5	0	0	0	0	0	1	1
Village 6	0	0	0	0	0	0	1

##### 

**Randomization** Before the beginning of the implementation process, clusters will be randomly allocated a time when they are going to receive the intervention. According to the CONSORT guidelines extended to cluster randomized trials, the statistician will randomize the cluster using computer generated random numbers [27]. Only the research team will be aware of the allocation of all of the clusters. In order to keep allocation concealment, village inhabitants will be informed of the allocation time at the moment of the implementation in their cluster.

Due to the nature of the intervention, it will be not possible to blind inhabitants to the intervention. However, outcomes will be assessed by a different fieldwork team blinded to the intervention.

##### 

**Periodical assessments** These will include data collection regarding costs and clinical measurements. Every five to six months, once a new village commences on the intervention, a new evaluation will be performed in all participant villages, both intervention and control. Clinical measurements will include systolic and diastolic blood pressure, height, and weight. These periodic assessments will be performed at each household to guarantee contact with each family member enrolled in this study.

##### 

**Cost-effectiveness analysis** For this component, we will be interested in total cost of the implementation, including costs of the substitute itself and other associated costs due to transportation, delivery, and consumption frequency. We will also evaluate costs associated with the marketing and engagement campaign as well as capital costs. Information will be collected at the baseline but also in each of the periodic assessments. Thus, an incremental cost-effectiveness analysis as well as the additional cost to avoid an increase of 1 mmHg at the population level will be performed, comparing to the cost of using ordinary salt. This involves the estimation of the discrepancy in costs between the two contexts, ordinary salt and salt substitute consumption, and the difference of mmHg increase in each case.

